## Abstract

**Background:**

In collaboration with building developers, the Housing for Health team is contributing to the design of community-based congregate living facilities to support healthy living in older adults. There may also be opportunities to improve the surrounding neighbourhoods by collaborating with the municipalities where the developments are located. We will evaluate whether one or more of these comprehensive interventions lead to changes in the perceived, microscale, and macroscale neighbourhood-built environment (BE) and amenities, and impacts on the physical activity (PA), healthy eating, and social connections of residents. In parallel, we will gather qualitative data to provide a more in-depth understanding of how the BE may facilitate or hinder resident’s healthy living outcomes.

**Methods:**

This project employs a quasi-experimental pre-post design with at least one or more intervention and control sites. The quantitative BE evaluation will include pre- and post-intervention assessments of neighbourhood macroscale (e.g., layout of communities) and microscale (e.g., street details and characteristics) changes using Geographical Information Systems (GIS) and Microscale Audit Pedestrian Streetscapes (MAPS) audits, respectively. The quantitative resident evaluation will include self-report (i.e., surveys) and objective assessments (i.e., accelerometers, Global Positioning System [GPS]) of residents at baseline (3-6-months pre-move-in) and follow-up (3-6-months and 9-12-months post-move-in if possible). The qualitative resident-environment component will involve in-depth semi-structured interviews post-intervention with building residents, family members, and stakeholders involved in the design/development and/or operation of the intervention site(s). Participant observations will be completed in the building and neighbourhood environments of the intervention site(s).

**Discussion:**

Findings will provide evidence on whether and how comprehensive changes to the BE and amenities of at least one congregate living facility and the surrounding neighbourhood can impact PA, healthy eating, and social connections of older adults. Successful intervention elements will be scaled up in future work. We will disseminate findings to a broad audience including the scientific community via peer-reviewed publications, conference presentations, and discussion panels; and the private, public, and not-for-profit sectors via reports, public presentations, and/or communications via our partners and their networks.

**Trial registration:**

Protocol ID: 1819-HQ-000051. ClinicalTrials.gov ID: NCT05031273. Registered 29 June 2021 with ClinicalTrials.gov.

## Background

Engaging in regular physical activity (PA), eating healthily, and being socially connected contribute to quality of life, and prevention and management of disease throughout the older years [1–3]. Engaging in aerobic PA of moderate or higher intensity also helps older adults maintain their functional independence longer [4]. Unfortunately, many older adults are insufficiently active. Only 17% of Canadian adults aged 60–79 years meet recommended guidelines, as determined by accelerometers [5]. Rates of social contact also substantially decrease in older age [6], and many do not consume sufficient amounts of fruits and vegetables [2]. Additionally, as the proportion of the global population aged 60 years and older is expected to double to 2.1 billion by 2050 [7], associated health care costs are of concern. Thus, public health interventions designed to support healthy living in older adults are imperative, to ensure both quality of life for growing older populations, along with reducing costs of healthcare [8].

Older adults are important contributors to our communities; yet they require additional supports to help deal with inevitable physical and social changes that occur with aging [9]. In response to global aging, the World Health Organization (2007) is promoting the creation of “age-friendly communities”, which includes designing housing and physical environments to meet needs in people of all ages, supporting the wellbeing of older residents, and ensuring cities are thriving. As many older adults are retired and tend to spend more time within their home and neighbourhood, the design of communities may be particularly important for this population [10].

According to the ecological model of age-friendly communities [11], a constellation of physical and social factors in the interpersonal, community, and policy environments interact to either support or hinder health in individuals. Consistent with this model, a recent review of the literature concluded that neighbourhoods that promote overall PA in older adults are those that are safe and walkable, with aesthetically pleasing scenery and access to destinations and services [12]. Different features however may be important for different types of physical activities. Kerr, Rosenberg [10] proposed that access to destinations, connectivity of streets, and access to transit are likely the most important factors for transportation walking, whereas safety, aesthetics, and parks are more important for recreational walking. As many older adults live in congregate living developments, it is also important to understand how features of these buildings and surrounding sites can support or hinder the healthy living of residents [13]; yet much of the research to date has focused on the outdoor neighbourhood built environment (BE).

Given the decline in mobility and physical function associated with aging, accessibility to healthy food options (e.g. fresh fruits and vegetables) within a walking distance is crucial for healthy aging [14]. Diet quality among urban dwelling older adults has been shown to be associated with the proportion of fast food outlets and stores selling healthy foods [15]. BE elements can also enhance social connections in older adults with ramps to access buildings linked to perceived social connectedness [16].

Although evidence is accumulating on the importance of the BE for healthy living in older adults, much of the research is cross-sectional, and does not allow for establishment of temporal precedence [17]. Many also do not rule out alternative causal explanations (e.g., residential self-selection). To provide stronger evidence for the importance of the BE for healthy living, researchers have started to evaluate impacts of BE interventions on health outcomes [18, 19]. Such designs are vital as they allow us to isolate the effect of the BE on healthy living, and allow for conclusions around causality [17]. Because randomized control trials are difficult to implement in real-world community settings, quasi- and natural-experiments are important research designs in public health [20]. To date, short-term urban and landscape street design interventions have resulted in changes to perceptions of walkability and street safety, and perceptions of being more active post-intervention, with no change in social engagement or outdoor activity [21, 22]. An urban greenspace intervention however did not impact well-being behaviours and use of the spaces by older adults [23]. Given that the environment includes many features, multiple co-occurring interventions may be necessary to produce meaningful impacts on behaviour [24]. Interventions may also be more effective if they are designed based on consistent correlates identified in the literature [24].

Gathering information on intermediate variables can help provide understanding around the pathways between the BE and health outcomes [17]. The Capability, Opportunity, Motivation, and Behaviour (COM-B) model represents a behavioural system of factors (i.e., beliefs) that interact and reciprocally influence health-related behaviours [25]. The antecedents of behaviour include perceptions of psychological (e.g., ability to reason and comprehend) and physical capability (e.g., physical strength and skill), social (e.g., cultural and linguistic factors) and physical opportunity (e.g., BE), and motivation which includes reflective (e.g., conscious decisions) and automatic processes (e.g., habits, emotional reactions). This behavioural system is linked to intervention functions and policy categories via the behaviour change wheel, with “environmental restructuring” being the critical function for our study.

The Designing Communities to Support Healthy Living in Aging Residents Study is designed to address several of the aforementioned gaps in the literature. This study is a part of the Housing for Health project, which is a five-year initiative (2018–2023) in Alberta, Canada that investigates how the BE of housing developments and neighbourhoods supports health and protects against disease. In collaboration with building developers, the Housing for Health team is contributing to the building and site design of community-based congregate-living facilities to support healthy living in older adults. The team is also meeting with the municipalities where the developments are located to explore opportunities to improve the surrounding neighbourhoods. To evaluate the impacts of one or more of these comprehensive interventions, we will audit the microscale and macroscale BE to document implemented design and amenity elements, along with changes that occur due to factors outside of the study. We will then examine whether and how these design and amenity elements impact the residents’ healthy living outcomes and perceptions of neighbourhood built and food environments. In parallel, we will gather in-depth understandings of how the BE may facilitate or hinder resident’s healthy living behaviours using qualitative methods.

The quantitative environment evaluation will examine the following objectives.

To assess whether microscale and macroscale neighbourhood BE features and amenities supporting PA, healthy food consumption, and social connections at the intervention site(s) descriptively appear to have changed more than control site(s).To assess whether macroscale neighbourhood BE features and amenities impacting PA, healthy food consumption, and social connections are more supportive in the intervention site neighbourhood(s) post-intervention compared to the residents’ old neighbourhoods.

The quantitative resident evaluation will examine the following objectives.

3)To assess whether residents from the intervention site(s) have greater improvements in PA, healthy food consumption, and social connections, compared to residents from control site(s).4)To assess whether perceived built and food environments of residents improve more in the intervention site(s) compared to control site(s).5)To assess whether change in capability, opportunity, and/or motivation mediate the effect of the intervention on changes in PA, healthy food consumption, and social connections.

The qualitative resident-environment component will explore the following objectives.

6)To document detailed features of the BE and people-BE interactions at the intervention site.7)To gather insights on how the BE at the intervention site impacts residents’ PA, healthy food consumption, and social connections through capability, opportunity, and motivation.

## Methods/design

### Study design

The quantitative component will follow a quasi-experimental pre-post design as the assignment to groups is non-random and our research team is working with developers and municipalities to influence the interventions. However, uptake of suggested building and site scale recommendations is ultimately up to the discretion of the developers and architects, and uptake of neighbourhood-scale recommendations is ultimately up to the discretion of the municipalities.

### Setting and residents

The evaluation will include at least one intervention site and one or more control site (we are aiming for two or more) situated in Edmonton and nearby towns in northern Alberta, Canada. This region experiences long, cold, and icy winters, and mild to hot summers.

The intervention site(s) will be planned upcoming community-based congregate living building(s) where our team has the potential to influence design and amenities of building(s), site(s), and/or neighbourhood(s), and where an evaluation of the impacts of moving into the new building(s) on resident’s healthy living outcomes is possible during the timeframe of the grant (October 2018 to October 2023). The units may be rental or life lease units. We plan to select standard community-based congregate seniors housing with few health-promoting features as control site(s). The intervention and control sites will be as closely matched as possible on city (e.g., size), building (e.g., building type, number of stories, number of independent living units), and resident demographics (e.g., age, income). The timelines for construction are controlled by the developer(s), and dependent on many external factors (e.g., approvals from the municipality, grant funding or loan approvals, COVID-19-related factors, availability and cost of building materials and supplies). Therefore, exact locations of the intervention and control site(s) are still being finalized to ensure we can complete the evaluation research within grant timeframes. Several delays have already occurred.

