#### Analyses

Differences in baseline characteristics (e.g., demographic factors and outcome measures) of residents in the intervention and control site(s) will be investigated using independent samples t-tests. Any differences identified may be considered as covariates in the main analyses. We will attempt to control for any unusual events and socio-economic or political influences that occurred during the study period. Covariates may include age, gender, building site, functional ability, car ownership, socio-economic status or other demographic variables that differ between residents of intervention and control sites at baseline.

We intend to run a difference-in-difference analysis to test for differences between intervention and control groups in change from baseline to 3-6-month post-move-in, and change from baseline to 9-12-month post-move-in. The type of analysis will depend on the measurement unit of each outcome (e.g., linear regression for continuous outcome variables, logistic regression for categorical outcome variables). For the primary outcome of PA, a difference-in-difference linear regression analysis with a continuous outcome will have 80 % power with 107 participants for a model with five main predictor variables and three covariates at α = 0.05 [53].

Depending on how many units the final intervention and control sites have, data may be collected on couples and a multi-level modeling approach used to control for clustering within unit. The approach that is best able to maximize power will be chosen.

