## Discussion

This project will provide valuable information on whether partnering with developers, site design teams, and municipal officials can result in comprehensive and meaningful changes to the perceived, microscale, and macroscale BE of at least one community-based congregate living facility and the surrounding neighbourhood. Additionally, it will show whether comprehensive changes to the BE can have an impact on the healthy living outcomes of older adults. Quantitative and qualitative findings are expected to be used by practitioners such as architects, landscape architects, planners, property developers, and municipalities to understand how the BE can be improved to support older residents’ healthy activities in future projects and policies. In the future, our team plans to scale up this work to similar settings, as well as to expand this work to other populations (e.g., populations with other socio-economic circumstances). Findings will be disseminated to a broad audience including the scientific community, private, public, and not-for-profit sectors, and community residents via peer-reviewed publications, non-academic reports, academic and practitioner conference presentations and discussion panels, public presentations, news media interviews, and communications with our partners and their networks. The Housing for Health team currently has over 200 partners from multiple sectors in Alberta and across Canada, including academics, developers, architects, urban planners and designers, city officials, and community groups.

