To gather greater evidence on the causal impacts of the BE on healthy living, it is now recommended that researchers in this area focus on research designs that support causal inferences, such as quasi-experimental studies [24]. Therefore, the quasi-experimental pre-post design is a key strength. The comprehensive intervention, including potential improvements at the building, site, and/or neighbourhood scales, is a benefit as many BE interventions are focused on small scale changes (e.g., to the street design), which may not be sufficient to change behaviour. The use of theory to guide this work is also an important strength as it has allowed us to identify key intervention mechanisms to test. Use of both objective and self-report measures of PA is a strength as accelerometers and GPS devices provide data that does not rely on participants’ memory recall, whereas self-reported PA can capture PA in different settings (e.g., exercise class, gym attendance). We will also measure total PA which captures PA required for optimal health benefits, along with domain-specific PA which can provide information on the types of PA influenced by the intervention. Behavioural specificity of outcomes is important as different features of the environment may increase some types of PA but not others [10]. Objective measurement of the BE and food environments using macroscale and microscale assessments along with survey measurements is also a strength as different people perceive the BE in different ways, and these perceptions will not always be consistent with objective assessments [57]. Finally, complementary qualitative work is an important strength as it will provide a more in-depth understanding of the factors that influence residents PA, healthy eating, and social connections within the BE.

The study has limitations that should be mentioned. As it will be conducted in Alberta, Canada and may only include one intervention site with participants of a particular socio-economic status, findings may not generalize to older adults in other socio-economic situations or living in other regions. Although we will work for saturation and depth of data from qualitative interviews, we expect the number of interview participants to be relatively small. Therefore, we will not be able to capture the lived experiences of all residents.

The Housing for Health website [58] provides an overview of the entire project that the study is a part of.

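### With possibly one building per arm, building-specific change cannot be separated from the intervention, and neither the resident-level analysis nor the 107-participant power statement allows for it

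*Protocol article*

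**What the plan says.** Setting and residents sets the minimum at "at least one intervention site and one or more control site (we are aiming for two or more"; the aim of two or more refers to control sites. Study design describes a "quasi-experimental pre-post design as the assignment to groups is non-random". Under Intervention, the design elements apply to the building, its site and the neighbourhood, and are tailored to each location.

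Under Quantitative resident evaluation, Analyses, the authors write: "We intend to run a difference-in-difference analysis to test for differences between intervention and control groups in change from baseline". The same section states 80% power with 107 participants at α = 0.05, for a model with five main predictors and three covariates. On adjustment: "Covariates may include age, gender, building site, functional ability, car ownership, socio-economic status" and other demographic variables. On clustering: "data may be collected on couples and a multi-level modeling approach used to control for clustering within unit", with the choice of approach to be made on power. No other level of clustering is named.

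Under Procedures, baseline is 3 to 6 months before move-in and follow-up is after move-in.

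The Discussion says that "it will show whether comprehensive changes to the BE can have an impact on the healthy living outcomes of older adults". Its limitations paragraph raises the single site only as a limit on generalisability: the study "may only include one intervention site with participants of a particular socio-economic status, findings may not generalize".

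**The concern.** The unit that receives the intervention is the building, while the unit of analysis is the resident. Anything particular to one building after move-in, such as its manager, its social programme or how it applied local COVID-19 rules, moves all its residents' outcomes together. If each arm has one building, such an influence looks exactly like an intervention effect.

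Difference-in-differences removes a building effect only if it is the same before and after. Intervention residents live elsewhere at baseline, so the new building's effect is absent before and present after, and it passes straight into their change score. Control residents already live in their building, so a stable effect cancels there, but a change in that building between visits does not.

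What is at stake is how the primary physical activity result is read. A resident-level interval describes the difference between these particular buildings. Read as evidence about health-promoting design, it is too narrow for any positive building ICC.

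**Working it through.** **Step 1: the plan's own figure.** Inputs from Analyses: N = 107, 5 + 3 = 8 model terms, α = 0.05, power 80%. The article gives no effect size, so f² = 0.15 is assumed. Take the overall F test of all 8 terms with independent observations, noncentrality λ = f² × N, and 8 and N − 9 degrees of freedom. This requires N = 109, and power at N = 107 is 0.7945. The stated figure is therefore approximately reproduced; f² = 0.1517 gives exactly 80% at 107. At f² = 0.15, testing 5, 3 or 1 of the 8 terms would require 92, 77 or 55. A different effect size could bring any of these to 107, so the match does not prove which form was used. None of the forms contains a building term, and the article states no design effect.

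**Step 2: what building site does as a covariate.** This was checked by the rank of the design matrix.
- Change-score model, one versus one: the site indicator and the group indicator are the same column, so group cannot be estimated once site is entered.
- Stacked pre/post model with a site main effect: group-by-time remains estimable. With every resident measured at both times, the estimate is the same with and without the site term.
- Stacked model with site-by-time: group-by-time is not estimable.

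No form both keeps the group contrast and adjusts it for site-specific change.

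**Step 3: size of the understatement.** Let ρ be the ICC of the change score within building (assumed, equal in both arms). Let n_A and n_B be the arm sizes, and S the sum over both arms of squared within-arm site shares. Then

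variance ratio = [(1 − ρ)(1/n_A + 1/n_B) + ρS] / (1/n_A + 1/n_B)

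actual type I error = 2 × [1 − Φ(1.96 / √ratio)]; effective N = 107 / ratio.

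Example, one versus one, ρ = 0.02, sites of 54 and 53: 1/54 + 1/53 = 0.03739 and S = 1 + 1 = 2. The ratio is (0.98 × 0.03739 + 0.04) / 0.03739 = 2.05. The standard error is √2.05 = 1.43 times the reported one, and 2 × [1 − Φ(1.96/1.43)] = 0.17.

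| Sites (residents) | Between-building df | Assumed ρ | Variance ratio | SE ratio | Type I error | Effective N |
|---|---|---|---|---|---|---|
| 1 v 1 (54; 53) | 0 | 0.01 | 1.52 | 1.23 | 11% | 70 |
| | | 0.02 | 2.05 | 1.43 | 17% | 52 |
| | | 0.05 | 3.62 | 1.90 | 30% | 30 |
| 1 v 2 (36; 36, 35) | 1 | 0.01 | 1.35 | 1.16 | 9% | 79 |
| | | 0.02 | 1.70 | 1.30 | 13% | 63 |
| | | 0.05 | 2.74 | 1.66 | 24% | 39 |

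Degrees of freedom are the number of sites minus 2. At one versus one, building variance cannot be estimated from the data. Nor do more residents cure it: as n_A and n_B grow, the variance of the contrast tends to 2ρ (in units of the total variance), not to zero.

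**The case against.** The authors take real steps against site differences. Sites are to be matched as closely as possible on city, building and resident demographics. The team will try to control for unusual events, and the audits will record changes arising outside the study. All sites lie in one region, so weather is largely shared. Part of what might be called a building effect is the intervention itself, since it is a tailored package that includes existing neighbourhood features. The number of sites depends on developers, and two or more controls are the aim. These points reduce likely bias and stand as such. They do not supply a between-building error term, and with one site per arm an event confined to one site is collinear with group-by-time, so it cannot be adjusted for.

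Fuller variance handling may sit in a document not shown. But the article does state its clustering level, its rule for choosing the approach and its covariate list, and the point rests on those.

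Three stronger readings are not supported:
- A reader might take the Discussion as promising a positive effect. It promises an answer to whether there is one. The difficulty is attributing that answer to design.
- A reader might infer that naming building site makes the planned analysis impossible. It is only a possible covariate, and as a main effect in a stacked model it is harmless, though of no use. With two controls, the rank deficiency of a change-score model holding group and all non-reference site indicators reflects one redundant indicator; contrasts between site means remain estimable.
- A reader might take 30% as the study's actual error rate. It belongs to one assumed ICC and to the minimum layout.

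**Conclusion.** The point holds. As stated, neither the analysis nor the 107-participant power statement allows for building-to-building variation in change. At one building per arm, such variation cannot be separated from the intervention. The limitations treat the single site only as a matter of generalisability, whereas it also affects internal validity.

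The direction is certain for any positive building ICC: resident-level intervals are too narrow when read as evidence about the intervention. The size is not known. The ranges of 11% to 30% (one versus one) and 9% to 24% (one versus two) rest on assumed ICCs of 0.01 to 0.05, near-equal sites, a total of 107 residents, no covariates and a normal approximation. The figure of 107 is not shown to be miscalculated. It is conditional on the buildings, and the article does not say so.

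**What to change.** **(a) Analyses.** Do not enter building site alongside group as an adjustment covariate. With two or more control sites, use site indicators in place of group and report the intervention site against each control separately. Add the control-versus-control contrast on the same outcomes as a descriptive yardstick for building-to-building variation. With two controls this is a single noisy contrast, so it should not serve as a formal test.

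**(b) Analyses and power statement.** State that resident-level intervals, p-values and the 80% power with 107 participants are conditional on the buildings studied and carry no allowance for variation between buildings. Add a sensitivity analysis that widens the intervals over a stated range of assumed ICCs.

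**(c) Discussion.** Add to the limitations that, with one site per arm, building-specific change cannot be separated from the intervention. Narrow the sentence on what the study will show to a comparison of these sites.

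These are changes to analysis and wording and need no data beyond those already planned. The cost is a more modest causal claim.
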